### Intervention fidelity

The extent to which facilitators deliver the intervention as intended (i.e., intervention fidelity) will be assessed based on a refined protocol from previous *Dove Confident Me* trials [36, 37]. Approximately half of the lessons, which will include various lesson facilitators and a range of student grades, will be assessed in real time by a trained fidelity assessor (a member of the Cimigo team) ensuring each lesson facilitator (i.e., teacher or guidance counsellor) is assessed at least once. In addition, approximately 50% of lessons will be video recorded (25% of lessons assessed in real time and 25% of lessons not assessed) to allow for additional checks by a second trained fidelity assessor (either a member of the research team fluent in Bahasa Indonesia or a member of Cimigo) for the purposes of establishing inter-rater reliability via intra-class correlations (ICC) for 25% of the lessons. These will be interpreted based on established criteria: ICC values less than 0.5 to indicate poor reliability; values between 0.5 and 0.75 to indicate moderate reliability; values between 0.75 and 0.9 to indicate good reliability; and values greater than 0.9 to indicate excellent reliability [64].

A standardised checklist prepared by study researchers will be followed, whereby fidelity assessors will check off the tasks and activities as outlined in the teacher guide as they happen during the lesson. Fidelity assessors will also note how long each of the six lesson sections takes the teacher to deliver. Furthermore, fidelity assessors will assess 12 teacher characteristics deemed important for effective delivery using five-point Likert-type scales from 1 (not at all) to 5 (very much). Example characteristics include “ideas expressed clearly” and “demonstrated enthusiasm for the material”. Fidelity assessors will rate on a 10-point Likert-type scale the extent they think the learning outcomes were achieved from 1 (not at all) to 10 (very much so). Finally, fidelity assessors will report if there were any deviations from the teacher guide or technological difficulties during the lessons.

### Procedure

Following randomisation, teachers and/or school guidance counsellors at the intervention-assigned schools delivering the intervention will be provided with access to UNICEF’s LSE e-module training curriculum to work through the body image lesson content at their own pace, as well as two 90-min live online training sessions (provided by author CR) via a video-conferencing platform. Teachers in the lessons-as-usual wait-list control group-assigned schools will be offered the training following the completion of the trial.

After parental/guardian consent is obtained and student assent is provided, students participating in the trial will complete an online survey on their own electronic device via Qualtrics software at three time points: T1 (pre-intervention), T2 (post-intervention), and T3 (two-month follow-up). Each survey will comprise the measures previously detailed in addition to some random attention-check items, with each survey expected to take approximately 30 min to complete. Survey data collection will be online in class groups led by a researcher via a video-conferencing platform. Only the lead researcher and teacher will be requested to have their videos on for this task. Students can choose whether they want their videos on or off. The researcher will verbally confirm student assent before explaining the format of the survey; the class teacher will also be online to support the process. Students will be expected to stay online while they complete the survey in a separate browser window on their device, and the researcher will be available to answer any questions via a private text function. Teachers will ensure only students with parent/guardian consent are present at each data collection time point in both conditions.

At intervention-allocated schools, participating students will take part in *Dove Confident Me Indonesia: Single Session* in groups of 20–30 students 1 week after completing the T1 online survey assessment. The lesson will take place via a virtual live class setting using video-conferencing software during school time and teachers will be responsible for ensuring only students with parent/guardian consent attend. Teachers may deliver the lesson to multiple groups of students at their school. Fidelity assessors will be present at approximately half of the lessons. Teachers will be requested to have their videos on during the lesson to enhance engagement. Bandwidth allowing, students will be invited to have their video on to simulate an in-person classroom environment, though they will be shown how to turn off their self-display if they would prefer to not see themselves throughout the lesson. Prior to the lesson, all students will be sent paper copies of the student worksheets via courier. Student survey acceptability feedback will be completed online at the end of their T2 assessment. Teacher acceptability feedback via an online survey will be completed after delivering the lesson on the same day or at a maximum of up to 1 week later. Student acceptability online focus groups will take place within a week following the T2 survey. Teacher acceptability online focus groups may take place before or after the T2 survey depending on scheduling.

At wait-list control-allocated schools, participants will complete the three assessments (T1, T2, and T3). After T3, teachers will be offered the lesson training and students will be provided with the lesson materials. Teachers can decide a suitable time to schedule the lesson.

All adolescents involved in the trial will be provided an electronic copy of a debrief sheet, which includes sources of support (Additional file 4: Debrief Sheet) and will be informed to contact their teacher or school guidance counsellor should they have any concerns in line with usual school procedures. All participating adolescents, teachers, and schools will receive a certificate on behalf of all research partners for their contribution to this research upon the completion of the trial. See the schedule of enrolment, interventions, and assessments in Fig. 2. The recommended Standard Protocol Items: Recommendations for Interventional Trials (SPIRIT) 2013 checklist with items to address in clinical trial protocols is provided as Additional file 1.

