### Study design

The main study consists of a two-arm open parallel group cluster RCT with an intervention group and a lessons-as-usual wait-list control group. Stratifying based on school size (large, medium, small), randomisation of schools will be conducted by an independent researcher blinded to conditions through block randomisation, using random block sizes of two, four, and six. Randomisation of schools will be completed following confirmation that schools recruited to the trial meet eligibility criteria, and the school principal has provided informed consent.

Cimigo and the study research team (i.e., study authors) will be informed of the study allocation, though will be blind to the size of each block during randomisation to minimise selection bias [56]. Participants will not be explicitly told their study condition, though will be made aware of the assessment time points and whether they receive the lesson between T1 and T2 (intervention) or after T3 (wait-list control). The statistician will be blinded to conditions during the trial and analysis. The trial will have assessments at baseline, post-intervention, and two-month post-intervention time points; see Fig. 1 for a flow diagram.

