#### Primary outcome measure: Body esteem

The primary study outcome will be body esteem, a specific component of body image, defined as a person’s self-evaluation of one’s body or appearance [59]. Body esteem will be measured using a culturally adapted Bahasa Indonesia version of the Body Esteem Scale for Adolescents and Adults (BESAA) [59]. Specific items and subscales to be used during the analyses will depend on the findings of the psychometric testing of the measure, as previously described. The self-report items are rated on a five-point Likert-type scale from 1 (never) to 5 (always). Negatively worded items are reverse scored and higher mean scores indicate greater body esteem.

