### Intervention acceptability

Quantitative and qualitative intervention acceptability data will be collected from students and teachers in the intervention condition. Acceptability questions, adapted from the *Dove Confident Me: Single Session* UK trial [36] will be incorporated into the post-intervention (T2) assessment survey. First, students will be asked to rate the lesson using a five-point Likert-type scale from 1 (strongly disagree) to 5 (strongly agree) on perceived enjoyment, helpfulness, understanding, comfort, teacher competence, topic importance, the likelihood to take future action to improve body confidence in themselves or others, and whether they will recommend the lesson to a friend. Second, students will be invited to provide free-text responses on what they liked most and least about the lesson, as well as their preference regarding the number of body image lessons using a three-point Likert-type scale (i.e., “I would like more sessions on body image”; “I think one session on body image is enough”; and “I think we do not need any sessions on body image”). Third, they will be asked what they perceived as the key messages of the programme via a free-text response to assess whether the learning objectives were understood. Fourth, students will be asked to rate the acceptability of the online delivery format of the lesson on a three-point Likert-type scale (i.e., “I had a good connection”, “My connection was okay”, and “I had a poor connection”). Finally, a free-text option will also be provided to describe any connectivity issues they might have experienced.

Teachers delivering the lesson will be asked to complete a short acceptability questionnaire online to capture their perspective of the programme in terms of the relevance of the topic for their students, adherence to the content, student engagement, and perceived student understanding. Then, in-depth acceptability data will be obtained from a subset of students (approximately *n* = 16) in a series of single-gender online focus groups (2 x focus groups with girls; 2 x focus groups with boys) led by a trained researcher. Similarly, a subset of teachers (approximately *n* = 6) will participate in an online acceptability focus group. Schedules for both the student and teacher focus groups are presented in Additional file 3: Acceptability Focus Group Schedules.

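### Nothing keeps the teacher who delivered the lesson, or an assessor who observed it, out of the T2 and T3 survey sessions, an avoidable post-baseline difference between arms for self-reported outcomes

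*Protocol article*

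**What the plan says.** The Study design section describes a "two-arm open parallel group cluster RCT" with a wait-list control. On masking it says "Cimigo and the study research team (i.e., study authors) will be informed of the study allocation" and "The statistician will be blinded to conditions during the trial and analysis". For students it says "Participants will not be explicitly told their study condition, though will be made aware of the assessment time points", and they also know whether their lesson falls between T1 and T2 or after T3.

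The outcomes are self-report. For the primary outcome, body esteem, "The self-report items are rated on a five-point Likert-type scale from 1 (never) to 5 (always").

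The Procedure section sets one format for T1, T2 and T3: class groups on a video platform, led by a researcher, and "the class teacher will also be online to support the process". The lead researcher and the teacher are the only people asked to have their cameras on. Teachers also check at each time point that only students with parental consent attend.

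In intervention schools the lesson is given by teachers or guidance counsellors of that school, who may teach several groups. About half of the lessons "will be assessed in real time by a trained fidelity assessor (a member of the Cimigo team"). At the end of the T2 survey, intervention students also rate the lesson on items that include "perceived enjoyment, helpfulness, understanding, comfort, teacher competence, topic importance".

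The Procedure and Data monitoring and management sections state safeguards. Students answer in a separate browser window on their own device, may keep their camera off, put questions to the researcher by private text and create their own codes. Only one university's research team can open the survey accounts.

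**The concern.** The lesson teaches that body confidence, meaning high body esteem, matters, and it ends with students signing a commitment to promote it. By the timings in the pilot section, which follow the main trial, T2 comes one week after the lesson and T3 eight weeks after. If the adult who taught the lesson is on camera while students rate their body esteem, or if the session leader sat in on that lesson, some students may give the answer they think is expected. No control class can be in that position, because control teachers are offered training, and their students the lesson, only after T3.

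A shift of this kind would probably favour the intervention and would be read as part of its effect. The Limitations section discusses online delivery, the single city and the lack of an active control. It does not discuss who attends data collection.

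**Working it through.** **Step 1. Who can be present, by arm and time point.**

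| Session | Intervention school | Control school |
|---|---|---|
| T1 | Class teacher, who has not yet taught the lesson; leader has not observed it | Same |
| T2, T3 | Class teacher, who may have taught the lesson to this class; leader may have observed it | Class teacher who has not taught it; no lesson to observe |

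The format is the same in both arms. What can differ is the role that the people present have had in the lesson, and this can differ only after T1.

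**Step 2. Is the overlap realistic?** The Procedure section speaks of the class teacher for the survey and of teachers or guidance counsellors for delivery, so the two need not be the same person. Elsewhere the roles meet. Trained teachers identify eligible students and send the consent letters (Study setting and participant recruitment). Teachers alone hold the contact data used to arrange attendance at both lesson and surveys, and teacher codes are matched to their classes' data (Data monitoring and management). Overlap is plausible, but its frequency is not stated. The survey leader is described only as a researcher; that this is a Cimigo employee who observed the same class is possible, not stated.

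**Step 3. Does the analysis deal with it?** The models in Data analysis adjust for the baseline score. The cue is absent at T1, so the baseline score carries no information about it.

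**Step 4. What a shift would do, if it occurred.** The documents give no size, so this is an illustration only.

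Inputs from Sample size calculation: 1000 students per arm, d = 0.2, 20 schools, hence 2000/20 = 100 per school. Assumed: two-sided alpha 0.05, baseline correlation 0, intraclass correlation (ICC) 0 to 0.05.

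The plan's own figure first, without clustering: SE = √(2/1000) = 0.0447 SD; 0.2/0.0447 = 4.47; power = Φ(4.47 − 1.96) = 99.4%. This agrees with the stated excess of 95%.

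Now let the true effect be 0 and the arm-level reporting shift be b. With SE = √[(2/1000)(1 + 99 × ICC)], the chance of a significant result in favour of the intervention is 1 − Φ(1.96 − b/SE):

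| b | Share of d = 0.2 | ICC 0 | ICC 0.01 | ICC 0.02 | ICC 0.05 |
|---|---|---|---|---|---|
| 0 | 0% | 2.5% | 2.5% | 2.5% | 2.5% |
| 0.05 SD | 25% | 20% | 12% | 10% | 7% |
| 0.10 SD | 50% | 61% | 35% | 25% | 15% |

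Example for b = 0.10 and ICC 0.05: SE = 0.0447 × √5.95 = 0.109; 0.10/0.109 = 0.92; 1 − Φ(1.96 − 0.92) = 15%.

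Here b is the average over the whole arm. If the cue is present in a fraction f of intervention classes and moves answers there by s, then b = f × s; for example, s = 0.10 SD in half of the classes gives b = 0.05 SD.

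**The case against.** The case on the other side is substantial.

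- **Privacy.** Neither the teacher nor Cimigo can see answers, and students need not be on camera. This stands and lowers the risk. It does not take the lesson's deliverer off the screen, and the article does not say that students are told teachers cannot see their answers. That wording may exist in material not shown.
- **Same format, and knowledge in both arms.** A reader might infer that only intervention sessions are run by people with an interest in the answers. The text does not support that: Cimigo and the research team know every school's allocation, so this knowledge is present in control sessions too. Only the possible lesson role of those present differs between arms.
- **Teacher ratings.** A reader might infer that rating the teacher's competence colours the outcome answers. Those items come at the end of the T2 survey and are not described for T3, so they cannot prime earlier answers by order. The most that can be said is that the rating itself may be given while the person rated is present.
- **Unavoidable expectancy.** Students know whether they have had the lesson, and the trial is declared open with a wait-list control. Much of any reporting bias would remain whoever attends. This stands; the point concerns only the avoidable part.
- **Practical role of teachers.** They check consent, hold the contact data and are a contact for student concerns. Sending every teacher out of every session would cost more than is needed.
- **Level of detail.** Rotas and scripts are commonly left to the full protocol. However, the article itself fixes the teacher's presence and camera, and that is what needs qualifying.

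**Conclusion.** The point holds as a modest, avoidable weakness in how the T2 and T3 sessions are staffed. As written, the procedure allows the lesson's deliverer or observer to be present when intervention students report their outcomes. Control classes have no counterpart, and baseline adjustment cannot correct for it.

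The documents do not show that bias will occur, how often the overlap arises or how large an effect it would have. The figures above rest wholly on an assumed shift and an assumed ICC and show only that a small shift would matter next to a planning effect of 0.2 SD. A reader might conclude that the outcomes are invalid or that a favourable result could be put down to this cue. The documents do not support that, given the stated safeguards and the unknown overlap. This is a cheap improvement, not a flaw that undermines the trial.

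**What to change.** 1. At T2 and T3 in intervention schools, the supporting staff member should be someone who did not deliver the lesson to that class, where one is available. Otherwise the deliverer confirms attendance and consent, then turns the camera off or leaves before the survey opens. The same rule on teacher presence applies in both arms.
2. The researcher leading a T2 or T3 session should not have observed that class's lesson.
3. The leader reads one identical script in both arms, which tells students that teachers cannot see their answers.
4. Any remaining reporting bias is added to the Limitations section.

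The cost is minor rota work with existing school and agency staff, and slightly less teacher support during a survey of about 30 minutes. The researcher's private text function partly covers that. Teachers keep their consent-checking role.

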**Fig. 2 Fig2:**
[figure not shown]
Schedule of Enrolment, Interventions, and Assessments

**Fig. 3 Fig3:**
[figure not shown]
An Excerpt of the Teacher Guide Featuring the Introduction and Part of Activity One

**Fig. 4 Fig4:**
[figure not shown]
The Before-and-After Social Media Photos Provided for Students in Activity Three

**Fig. 5 Fig5:**
[figure not shown]
The First Two Role-Play Scenarios Provided for Students in Activity Four

### Ethics and permissions

This trial received ethical approval from the Universitas Indonesia (KET-1373/ UN2.F1/ETIK/PPM.00.02/ 2020) and the University of the West of England (HAS.20.05.174). Approval for field data collection in junior high state schools in Surabaya was attained from the Surabaya District Education Office. The approval process from the Surabaya District Education Office involved obtaining a research permit from Bakesbang (National Unity and Politics Office) Surabaya and Bakesbang East Java. The application for this permit was led by authors at the Universitas Indonesia (BEM and KN), supported by UNICEF, Cimigo, and the UK research team. This project is registered as a clinical trial via clinicaltrials.gov: NCT04665557.

### Data monitoring and management

Based on previous evaluations of iterations of *Dove Confident Me* [36, 37], the study procedure and intervention are considered to be low risk for participant safety. Therefore, it was decided that an independent data monitoring committee is not required. However, the research team will monitor the data quality for completeness, consistency, and plausibility throughout the data collection period.

Electronic consent data will be kept securely by Cimigo for a five-year period in line with the Universitas Indonesia’s ethical requirements; it will not be shared among the research team. All survey data will be securely entered online using University of the West of England-approved Qualtrics software. Unique codes will be created by adolescents in order to match their responses across time points. Teachers will be allocated unique codes based on their school and class to allow researchers to match teacher responses to their classes’ data. Personal data (e.g., names, WhatsApp numbers, email addresses) of participating teachers will be held by Cimigo only and will be deleted upon the completion of the trial. Personal data (e.g., linking names with WhatsApp numbers and email addresses) of participating students to coordinate attendance at the lesson and data collection time points will be kept by teachers only.

Survey data from participants will be stored directly on password-protected Qualtrics accounts accessible only to the University of the West of England research team. Once downloaded, data will be stored on university-approved secure cloud storage (i.e., OneDrive). As personal data will not be requested from adolescents, the survey data should be anonymous. However, the data will be screened for personal data collected inadvertently (e.g., in qualitative free-text response boxes). Any personal data will be removed from the dataset at the earliest possible stage. Once screened, data will be securely shared with project partners at the Universitas Indonesia via OneDrive.

Video recordings of the lesson used to complete fidelity assessments will be taken by Cimigo and will not be shared. Once the fidelity intra-rater reliability assessments are complete, these videos will be permanently deleted. Similarly, audio recordings from the acceptability focus groups taken by Cimigo will not be shared with the wider research team. Audio data will be transcribed in Bahasa Indonesia by Cimigo and any personal data (e.g., participant names) will be removed. The anonymised transcripts will then be shared with research team members fluent in Bahasa Indonesia (LAS, KN, and CR). Researchers will review the transcripts within a month of receipt and check any points of clarification with Cimigo, who will review the audio recordings. Once all transcripts have been approved, the audio recordings will be permanently deleted.

